## Abstract

**Background:**

Type-2 diabetes rates in First Nations communities are 3-5 times higher than the general Canadian population, resulting in a high burden of disease, complications and comorbidity. Limited community nursing capacity, isolated environments and a lack of electronic health records (EHR)/registries lead to a reactive, disorganized approach to diabetes care for many First Nations people. The Reorganizing the Approach to Diabetes through the Application of Registries (RADAR) project was developed in alignments with federal calls for innovative, culturally relevant, community-specific programs for people with type-2 diabetes developed and delivered in partnership with target communities.

**Methods:**

RADAR applies both an integrated diabetes EHR/registry system (CARE platform) and centralized care coordinator (CC) service that will support local healthcare. The CC will work with local healthcare workers to support patient and community health needs (using the CARE platform) and build capacity in best practices for type-2 diabetes management. A modified stepped wedge controlled trial design will be used to evaluate the model. During the baseline phase, the CC will work with local healthcare workers to identify patients with type-2 diabetes and register them into the CARE platform, but not make any management recommendations. During the intervention phase, the CC will work with local healthcare workers to proactively manage patients with type-2 diabetes, including monitoring and recall of patients, relaying clinical information and coordinating care, facilitated through the shared use of the CARE platform. The RE-AIM framework will provide a comprehensive assessment of the model.

The primary outcome measure will be a 10% improvement in any one of A1c, BP, or cholesterol over the baseline values. Secondary endpoints will address other diabetes care indicators including: the proportion of clinical measures completed in accordance with guidelines (e.g., foot and eye examination, receipt of vaccinations, smoking cessation counseling); the number of patients registered in CARE; and the proportion of patients linked to a health services provider. The cost-effectiveness of RADAR specific to these communities will be assessed. Concurrent qualitative assessments will provide contextual information, such as the quality/usability of the CARE platform and the impact/satisfaction with the model.

**Discussion:**

RADAR combines innovative technology with personalized support to deliver organized diabetes care in remote First Nations communities in Alberta. By improving the ability of First Nations to systematically identify and track diabetes patients and share information seamlessly an overall improvement in the quality of clinical care of First Nations people living with type-2 diabetes on reserve is anticipated.

**Trial registration:**

ISRCTN study ID ISRCTN14359671, retrospectively registered October 7, 2016.

## Background

It is well known that type-2 diabetes disproportionally impacts Indigenous/First Nations people across the world, including Canada [1]. Overall, the prevalence of type-2 diabetes in First Nations communities is 3–5 times higher than in the general Canadian population [2, 3]. First Nations populations experience a high burden of disease, complications, and comorbidity [1], which is compounded by suboptimal care in isolated or remote communities [4–6]. Moreover, First Nations communities consistently rank among the lowest on social determinants of health, eroding their capacity to adopt health-promoting conditions, navigate the health system and advocate for change [7].

**Table 1 Tab1:** RADAR Structure by the RE-AIM Framework

RE-AIM dimension	Brief definition of dimension	Approach	Data source(s)
Adoption	Willingness of community members to initiate an intervention	Qualitative approach	Document review
Reach	Into the target population(s) (e.g., First Nations members with T2D)	Quantitative approach	Registry/CARE analytics
Implementation	Intervention is implemented as intended, and consistently across communities	Qualitative approaches	Interviews, document review, field notes
Effectiveness	Determined by outcomes	Quantitative approach	Registry/CARE analytics Interviews
Maintenance	Intervention effects or sustainability over time	Qualitative approach	Document review

Integral to the delivery of organized diabetes care are the 5R’s: **R**egister (systematically tracking all patients); **R**elay (facilitate information sharing); **R**ecall (timely review and reassessment); **R**ecognize (screening/risk factors assessment); and **R**esource (support self-management) [8]. In Canada, there is a shift towards a more comprehensive chronic care model (CCM) [8], including in the management of type-2 diabetes. However, most people living in First Nations communities have limited access to regular primary care and specialist services required for CCM-consistent diabetes care [9], with most care delivered through federally funded, nurse-led homecare and community health programs [10]. Perhaps due to fragmented care, along with cultural and geographical barriers, and physician/nursing shortages in rural and remote communities, First Nations populations have poor diabetes-related outcomes, including high rates of dialysis, blindness, amputations and foreshortened life expectancy [3, 6].

Despite recognition of these barriers, transformations to improve type-2 diabetes care and outcomes among First Nations people have been slow. Systematic proactive organization of diabetes care for First Nations people with diabetes living on reserves is lacking in Canada [2]. Current practice guidelines and Aboriginal Diabetes Initiative’s in Canada call for innovative, culturally relevant approaches that rely on community-specific programs for people with type-2 diabetes developed and delivered in partnership with target communities [2, 8].

Information systems that allow for a comprehensive-based approach to care, such as electronic health records (EHRs) linked with diabetes registries, positively impact quality of diabetes care and reduce costs [11–13]. Furthermore, incorporation of professional support to fully leverage the infrastructure, through a care coordinator, has been shown to improve intermediate measures of cardiometabolic care (e.g., A1c, blood pressure, cholesterol) and many other processes of care (e.g., foot and eye care, chronic care coordination) compared to usual care, however delivered [9, 11–16]. Currently, few First Nations communities have the infrastructure, expertise, or resources to employ the 5R’s as part of their CCM based quality improvement strategies, particularly the foundation upon which all these efforts are built: the ability to systematically identify and track diabetes patients and share information seamlessly (i.e., **R**egister, **R**elay, **R**ecall). Thus, it is unknown whether these benefits apply to the Canadian context and specifically to remote, isolated and under-resourced First Nations communities. This is context for which the “Reorganizing the Approach to Diabetes through the Application of Registries” (RADAR) project was designed.

### Objectives

Our purpose is to describe the RADAR project. Our primary objective is to implement and assess the effectiveness of an integrated population based electronic health record (EHR)/registry system specifically designed for First Nations communities (*Community Assessment Response and Empowerment [CARE] platform),* coupled with dedicated support from a centralized care coordinator (CC) to systematically organize proactive diabetes care in the communities to improve diabetes-related outcomes. Thus, RADAR is the combination of the CARE platform and the CC support. We hypothesize that RADAR will result in an overall improvement in the quality of clinical care of First Nations people living with type-2 diabetes on reserve, as measured by evidence-based outcomes (A1c, BP, cholesterol) and quality of care indicators (e.g. foot and eye examinations). We believe that RADAR will help promote timely management of people with type-2 diabetes and increase diabetes knowledge and management practices among local healthcare workers [15, 17]. In addition, managers can use the EHR/registry to track diabetes trends, determine the effectiveness of diabetes programs, and assist in resource planning.

## Methods

### Model overview

The RADAR model incorporates two distinct elements: 1) an EHR, integrated with a population-based diabetes registry and analytics platform – *CARE platform*; and, 2) a centralized care coordinator. The CARE platform was designed by OKAKI Health Intelligence Inc. to meet the specific requirements of nursing-driven health programs currently being delivered on reserve in Canadian First Nations communities. Major limitations of existing EHRs, which are largely designed for physician offices, are: misalignment with programs, reporting and professional practice needs of service providers on reserve; no population-based registry that supports sharing between facilities and population (as well as individual) measurement and chronic disease management; and cost [18, 19].

The first element of RADAR, the CARE platform, specifically integrates a patient registry and electronic clinical chart for patients across three traditionally distinct and segregated programs responsible for care on reserves (Home and Community Care, Aboriginal Diabetes Initiative, and Community Health); thereby, improving coordination of care between service providers on reserve. The CARE platform includes a diabetes registry, enabling the systematic, standardized capture of patient data on key diabetes outcomes and quality of care indicators (e.g., A1c, BP, cholesterol, foot and eye exams); and incorporates performance-based measurement and reporting on clinical care standards and targets at both the population and individual level. The system also provides real-time recognition and recall of patients needing follow-up care. Moreover, the CARE platform uses a simple interface and can be accessed through a web-based portal allowing for remote monitoring and evaluation of care and reporting.

In our ongoing discussions with community leaders, most diabetes care tends to be reactive to clients seeking care rather than proactively in accordance with clinical practice guidelines. Many clients do not receive ongoing diabetes care and do not have a regular general practitioner who coordinates care. Thus, we have combined our CARE platform with a key facilitator – a centralized care coordinator (CC). The CC is ideally a First Nations registered nurse and certified diabetes educator with significant experience with care on reserve. The CC will work remotely with the local healthcare workers on reserve to improve quality of care for people with diabetes, facilitated through shared use of the CARE platform and web conferencing technologies. The CC supports systematic review of patients and case conferencing activities to support and prioritize care, problem-solves system or patient-level care issues, and provides education to local healthcare workers. In addition, the CC acts as a bridge between the First Nations communities and other service providers to help coordinate patient care on and off reserve. Together, both RADAR elements address the 5Rs in organizing diabetes care, that is, recognize, register, relay, recall, and resource, in the First Nations context. In addition, managers and researchers can use the analysis of population-level data for epidemiological assessments, quality-improvement, and decision-making.

### Setting

RADAR involves collaboration with several First Nations communities in Alberta, representing separate treaty areas across the province (continuous expansion of the RADAR model to additional First Nations communities is ongoing). We estimate that approximately 1000 people with type-2 diabetes currently reside in the pilot communities. All communities involved are several hours of travel from a major urban center, where the majority of diabetes specialist care services are located. Some communities have local family physician clinics, located just off reserve that also provide care for patients with diabetes; other communities have visiting family physicians on one or more days a week; while other communities have no local physician services, although services are available in neighboring rural communities. As a result, local, on-reserve, healthcare workers are the primary service providers delivering diabetes care and general health services for these populations. Prior to implementing RADAR, all communities were familiar with the CARE platform for the management of patient care within their respective communities.

### Outcomes

The primary outcome will be a 10% improvement in measures over the baseline control periods in any one of the following: A1c, BP, cholesterol. This is consistent with our previous Canadian work that considers a 10% improvement in any of these measures to be the minimally clinically important difference [20]. For patients who are already at ‘target’ for any or all three measures at baseline, we will consider persistence at target (i.e., maintain values within 10% of baseline) as also achieving the primary outcome. Secondary endpoints will address other areas of diabetes care and process indicators compared to baseline including: the proportion of clinical measures and tasks completed in accordance with Canadian Diabetes Association Clinical Practice guidelines (e.g., A1c, BP, cholesterol, foot and eye examination, receipt of vaccinations, smoking cessation counseling); the number of patients registered in CARE; and the proportion of patients linked to a health services provider. In addition, we are collecting detailed information to conduct a comprehensive economic evaluation, assessing the cost-effectiveness of RADAR specific to these communities. Our approach to the economic analysis will be analogous to methods previously published by our group [21, 22].

We will also conduct a qualitative assessment as part of our comprehensive evaluation to supplement the primary and secondary quantitative assessments. The purpose of the qualitative component is to provide contextual information, such as the quality/usability of the CARE platform and the impact/satisfaction of local healthcare workers with the CC model.

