### Intervention phase

After completion of the *Baseline Phase*, each community will transition into the *intervention phase* for a minimum of 1 year. The intervention phase will conclude on December 31, 2020, for all communities and length of follow-up is dependent on timing of initiation of RADAR within the community. During the intervention phase, the CC will help the local healthcare workers to proactively manage patients with type-2 diabetes, including monitoring and recall of patients, relaying clinical information and coordinating care, facilitated through shared use of the CARE platform and web conferencing technologies. In addition, the CC will provide support on the use of the CARE platform and training and education for the local healthcare workers on ‘best practices’ for the management of type-2 diabetes. It is expected that the local healthcare workers’ reliance on the CC will diminish over time, as they become more confident and competent using the CARE platform and in their diabetes knowledge and ability to manage patients, leading to sustainability.

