### Data analysis

For quantitative data, all relative changes will be analyzed using the last known recorded value from the CARE platform from baseline to the end of the intervention phase. We will employ an intention-to-treat analysis, whereby all patients who are enrolled and have baseline data will be included in our primary analysis. The primary endpoint (i.e., 10% improvement in any of A1c, BP, cholesterol values from baseline or those maintaining values within 10% of baseline if at any or all three targets at baseline) will be evaluated using a conventional intention to treat analysis with logistic regression. However, if the observed intracluster correlation coefficient (ICC) is non-ignorable, we will use generalized estimating equations (GEE) that accounts for the clustered and hierarchical nature of our data [24]. Several a-priori subgroup analyses are planned for the primary endpoint. First, we will restrict analyses to patients not at target for any of the 3 primary outcome measures. Second, we will restrict analyses to those patients who were at target for each primary outcome measure (A1c, BP, cholesterol) to fully examine persistence at target over time. Additional subgroups of interest include analyses stratified by sex, and analyses stratified by age (<65 vs > =65 years). Secondary endpoints include: the proportion of clinical measures completed in accordance with guidelines (e.g., A1c, BP, cholesterol, foot and eye examination, receipt of vaccinations, smoking cessation counseling); the number of patients registered in CARE; and the proportion of patients linked to a health services provider.

We anticipate not having complete quantitative data on all endpoints of interest, given the real-world implementation of the project. Several approaches will be used for missing clinical data. First, in alignment with the intention-to-treat approach, we will use the baseline observation carried forward technique for our primary outcome. The stability of the results will be additionally evaluated using the multiple imputation method as a sensitivity analysis.

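### With an any-one-of-three endpoint and baseline carried forward, the primary result depends on how many measures are re-tested, so testing is confounded with control

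*Protocol article*

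**What the plan says.** The Outcomes section defines the endpoint: "The primary outcome will be a 10% improvement in measures over the baseline control periods in any one of the following", the three being A1c, BP and cholesterol. It adds a second route for measures already at target at baseline: "we will consider persistence at target (i.e., maintain values within 10% of baseline) as also achieving the primary outcome".

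The Data analysis section sets the population, in which "all patients who are enrolled and have baseline data will be included in our primary analysis", without a minimum number of measures. It compares one last recorded value per measure with baseline. It expects gaps: "We anticipate not having complete quantitative data on all endpoints of interest". For these, "we will use the baseline observation carried forward technique for our primary outcome", and stability is to be checked "using the multiple imputation method as a sensitivity analysis".

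The Intervention phase section describes proactive management by the care coordinator and local workers, "including monitoring and recall of patients". Completing A1c, BP and cholesterol measurement according to guidelines is itself a secondary endpoint. One planned subgroup is patients not at target on the three measures.

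**The concern.** Each rule is ordinary alone. The difficulty lies in combining them with an intervention that changes how often patients are tested.

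Take a patient with stable disease. If a measure is off target and nobody repeats it, the carried-forward value shows no change and the measure fails. If it is repeated, ordinary variation or regression to the mean gives it some chance of a 10% improvement. Each further off-target measure that is re-tested adds another chance. For an at-target measure the direction is opposite: unrepeated, it counts as persistence by default, and a repeat test can only take that success away.

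So the composite responds to testing completeness in both directions. At stake is the reading of the primary result. The Discussion says that the aim is to learn whether RADAR can influence these clinical measures, and the composite alone cannot separate that from more complete follow-up. Communities also differ in length of follow-up, and hence in opportunity for re-testing.

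**Working it through.** **Inputs from the protocol article.** Usual-care rate 40% and target 50%, hence a 10-point effect (Power and sample size); any-one-of-three success and the at-target rule (Outcomes); baseline carried forward (Data analysis).

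**Assumptions, not in the article.** 40% is the any-of-three rate for patients with all three measures off target and re-tested. The article writes the three measures joined by *and*, so this is a reading. Components are independent and equally likely to improve, and all three have a baseline value. Let u be the share of measures re-tested, taken as 60% without and 90% with RADAR. Let t be the share at target at baseline. Let p be the chance that a re-tested off-target measure shows a 10% improvement, and q the chance that a re-tested at-target measure stays within 10%. Neither p nor q changes, so control is no better.

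**Step 1: recover the article's 40%.** 1 − (1 − p)³ = 0.40 gives p = 1 − 0.6^(1/3) = 0.157. With k off-target measures re-tested, success is 1 − (1 − p)^k: 15.7% for k = 1, 28.9% for k = 2, 40.0% for k = 3. Each further measure adds 13.2 or 11.1 points.

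**Step 2: more re-testing, nothing at target.** Success is 1 − (1 − u·p)³.
- u = 0.6: 1 − (1 − 0.0942)³ = 25.7%
- u = 0.9: 1 − (1 − 0.1413)³ = 36.7%

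The difference is +11.0 points. For p from 0.10 to 0.30 and rises in re-testing of 20 to 30 points, the gain is about 5 to 16 points.

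**Step 3: add the at-target route.** The chance that one measure succeeds is s = t·(u·q + 1 − u) + (1 − t)·u·p, and the composite is 1 − (1 − s)³. For p = 0.157, u from 0.6 to 0.9:

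| Share at target, t | Success at q = 0.7 | Change, q = 0.7 | Change, q = 0.6 to 0.9 |
|---|---|---|---|
| 0 | 25.7% to 36.7% | +11.0 | +11.0 |
| 0.1 | 42.2% to 48.8% | +6.7 | +6.2 to +7.6 |
| 0.2 | 56.0% to 59.3% | +3.3 | +2.4 to +4.9 |
| 0.3 | 67.4% to 68.3% | +0.8 | −0.5 to +2.9 |
| 0.4 | 76.7% to 75.8% | −0.9 | −2.5 to +1.5 |
| 0.5 | 84.0% to 82.0% | −2.0 | −3.8 to +0.6 |

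**Step 4: where the sign changes.** s does not depend on u when t·(1 − q) = (1 − t)·p, that is t = p/(p + 1 − q). For p = 0.157 this is 0.28 at q = 0.6 and 0.61 at q = 0.9. For p = 0.25 it is 0.38 and 0.71.

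**Step 5: relax independence.** A simulation of stable patients with correlated measures (0.2) and assumed within-person variation, again with re-testing from 60% to 90%, gave overall gains of 8 to 11 points at t = 0.05, 4 to 6 at 0.20, 2 to 3 at 0.35 and under 0.5 at 0.50. Among patients with no measure at target the gain was 10 to 16 points throughout.

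**Step 6: which rule does what.** With a single off-target measure, success goes from 0.6 × 0.157 = 9.4% to 0.9 × 0.157 = 14.1%, or +4.7 points. Carry-forward creates the dependence on testing, and the any-of-three rule enlarges it to +11.0.

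**The case against.** A reader might infer that more testing always raises this endpoint, so that a positive trial would show only better testing. The documents do not support that. An at-target measure needs no second test to count, and re-testing can only lower it. The 11-point figure is the limiting case of patients with nothing at target, not the whole analysis population. At about half of measures at target the shift is near zero, or slightly negative in the simple formula. Repeat tests of one measure add nothing either, because a single last value is used.

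Nor would it be right to say that testing and control can never be separated. Multiple imputation is already planned and would weaken the link between being tested and succeeding, and the values needed for component results are in the CARE platform. The absence of component tables from a condensed article is not a fault, since they may stand in a fuller plan. Choosing a composite is a legitimate design decision, for which the article gives a rationale.

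What stands is narrower. The endpoint, the analysis set and the primary missing-data method are all fixed in the article, and together they make the primary result depend on re-testing. Imputation is assigned only to a sensitivity analysis. The upward shift is largest in patients with no measure at target, which is how I read the first planned subgroup.

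**Conclusion.** The point holds in conditional form and should be dealt with before results are interpreted. Re-testing pushes the composite up through off-target measures and down through at-target ones, and RADAR is built to change re-testing. In patients with no measure at target, the shift without better control can be about the size of the planned 10-point effect. In the whole population it is smaller, and its sign depends on the share at target, which the article does not give. A rise in the composite therefore cannot be taken alone as better A1c, BP or cholesterol, and a flat composite could hide some improvement if many patients start at target.

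These sizes rest on reading 40% as the any-of-three rate, on independence or a correlation of 0.2, and on assumed re-testing, improvement and persistence rates. The mechanism follows from the stated rules and needs only that re-testing differs.

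**What to change.** Add to Data analysis:

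1. For A1c, BP and cholesterol separately, report the responder rate (10% improvement if off target at baseline, persistence if at target) among patients with both a baseline and a follow-up value, together with the proportion re-tested. Place these beside the composite.
2. State that the composite will be read as clinical improvement only if the planned multiple-imputation analysis and the component results agree with it. Specify that imputation is done for each measure before the composite is formed.
3. Show the composite among patients with all three measures paired, as a supportive analysis, and say that this group is selected by follow-up testing, which RADAR itself affects.

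Items 1 and 3 stand beside the intention-to-treat composite and do not replace it. Adjusting for the number of measures available at baseline would not remedy this, because the re-testing happens after baseline.

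The cost is a little more analysis of data already held, with smaller and selected samples in the paired analyses. The endpoint and sample size are unchanged.
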